## Abstract

**Background:**

Adolescents growing up in communities characterised by adversity face multiple risk factors for poor mental health and wellbeing. There is currently a scarcity of research on effective approaches for preventing and treating psychological distress in this population, particularly in humanitarian settings. The powerful impact of the home environment and family support is well known; however, approaches targeting the family are seldom developed or evaluated in such settings. We developed a brief family systemic psychosocial support intervention to be delivered through existing child protection systems with non-specialist facilitators. This paper outlines the study protocol for a randomised controlled trial of the intervention in Lebanon.

**Methods:**

We will conduct a single-blind hybrid effectiveness-implementation multi-site RCT comparing the locally developed systemic family intervention to a waitlist control group for families residing in vulnerable regions in North Lebanon and Beqaa governorates (including families of Syrian, Palestinian, and Lebanese backgrounds). Outcomes on a range of family, adolescent, and caregiver measures will be assessed at baseline (T0) and post-intervention (T1), and at a 3-month follow-up for the treatment arm (T2). Families will be eligible for the trial if they are identified by implementing organisations as being medium-to-high risk for child protection concerns and have one or more adolescent aged 12–17 who demonstrates significant psychological distress on a self-report brief screening tool. Families will be randomly assigned to a treatment or a waitlist control condition. Families in the waitlist condition will receive a group version of the programme after completion of the study, to allow us to assess feasibility, acceptability, and preliminary indications of intervention effects of this modality. The primary outcome is reduction in overall adolescent-reported psychological distress over time, with post-intervention (T1) as the primary endpoint. Secondary adolescent-reported outcomes include family functioning, psychosocial wellbeing, and emotional regulation difficulties. Secondary caregiver-reported outcomes include parenting style, family functioning, psychological distress, and emotional regulation difficulties.

**Discussion:**

This trial will provide the first assessment of the effectiveness of the family systemic psychosocial support intervention for use in Lebanon, with important implications for the use of systemic, low-cost, non-specialist interventions for this age range.

**Trial registration:**

Local registry:

National Mental Health Program, Ministry of Public Health, Lebanese Republic. Registered on 19 October 2021

Lebanese Clinical Trial Registry LBCTR2021104870. Registered on 13 October 2021

Global registry: ISRCTN ISRCTN13751677. Registered on 1 November 2021

## Background

Adolescence is a critical period for shaping future mental health and wellbeing, yet adolescents living in adversity, particularly those growing up in humanitarian emergencies, face myriad risk factors. These include increased family and community violence, poverty and associated daily stressors, limited educational opportunities, other protection concerns, and lack of access to adequate services. In addition to this, access to quality mental health services is often severely constrained due to multiple factors including limited number of mental health professionals, lack of availability of affordable care, and stigma.

Recently, research and practice have turned attention to innovative task-shifting approaches, whereby non-specialists are trained and supervised to deliver mental health and psychosocial support interventions, and provide referrals to specialist services for the smaller number of individuals requiring them. Evidence from an increasing number of trials for psychological interventions with adults [1] and children and adolescents [2] has shown that this can be a safe and effective way to increase accessibility of care.

Despite knowledge of the importance of nurturing environments for promoting good mental health and wellbeing for children into adulthood [3], and of the effectiveness of family therapy [4], limited programmes have been developed and tested to support families in low resource and humanitarian settings. A systematic review of the literature in 2017 [5] found only 32 parenting and family interventions evaluated in low- and middle-income countries. We updated this review in 2020 ([name], [name], [name], [name], [name], [name], [name], [name], [name]: A systematic review of the evidence for the effectiveness and implementation of family and parenting interventions in lower and middle-income countries for child and adolescent mental health, in preparation) and found 43 new studies; however, very few focus on the family as a whole, very few are evaluated in conflict-affected settings and/or in the middle-east region, and most are preventive rather than supporting families already identified as at-risk or in distress. No family-focused interventions have been trialled to date in Lebanon.

Through a series of collaborative workshops with non-governmental organisation, United Nations, academic, and governmental partners, alongside consultation with local and international experts and a Community Advisory Board (CAB) from the target communities, we developed a systemic family psychosocial support intervention designed to be delivered to families of at-risk adolescents through the existing child protection system in Lebanon. The intervention comprises six, 90-min family sessions, plus 30-min parent-only sessions each week, and a booster session 1 month later. The sessions target key family skills (described in methods) identified to be important through our extensive qualitative interviews with families, parents, adolescents, and experienced psychosocial support facilitators ([name], [name], [name], [name], [name], [name], [name], [name], [name]: Qualitative exploration of family functioning and mental health for at-risk adolescents in Lebanon, in preparation), and through analysing key intervention components and implementation models found in effective family interventions ([name], [name], [name], [name], [name], [name], [name], [name], [name], [name], [name], [name], [name], [name], [name]: development of the ‘Sawa Aqwa (Stronger Together)’ Family Focused Psychosocial Support Program for at-risk adolescents in Lebanon, in preparation). Key features of the intervention (referred to throughout as ‘family intervention’) include that it (i) involves the whole family; (ii) is transdiagnostic in nature, meaning that it targets families experiencing psychological distress broadly; (iii) is designed specifically for families living in communities characterised by adversity and acknowledges their lived reality; and (iv) can be safely delivered by non-specialists.

This paper presents the study protocol for the randomised controlled trial (RCT) being conducted in Lebanon to determine the effectiveness of the family intervention.

## Methods

### Design

The study is a single-blind type I hybrid effectiveness-implementation multi-site superiority RCT comparing the locally developed family intervention to a waitlist control group for families residing in vulnerable regions in North Lebanon and Beqaa governorates (including families of Syrian, Palestinian, and Lebanese backgrounds). Outcomes on family, adolescent, and caregiver measures will be assessed at baseline (T0) and post-intervention (T1), and at a 3-month follow-up for the treatment arm (T2). The primary outcome point is set as T1. The Standard Protocol Items: Recommendations for Interventional Trials (SPIRIT) is outlined in Fig. 1. A waitlist comparison condition was chosen in order to enable us to deliver a group-format version of the intervention with the control arm after T1 assessments are complete, to gather implementation data and experiences of this format.

**Fig. 1 Fig1:**
[figure not shown]
Standard Protocol Items Recommendations for Interventional Trials (SPIRIT): schedule of enrolment, interventions, and assessments. ^1^17-item screener. ^2^Daily stressors only

### Aims and hypotheses

The primary aim of the RCT is to assess the effectiveness of the family intervention on adolescent-reported symptoms of psychological distress at post-intervention. The secondary aim is to assess the effectiveness of the intervention using other measures of family functioning, parenting, and adolescent and caregiver mental health and wellbeing from pre- to post-intervention, and retention of effects in the treatment group at a 3-month follow-up timepoint. An additional aim is to explore possible treatment moderators (e.g. age, gender, past traumatic exposures, level of adversity, income). We will also explore whether treatment effects for adolescents and caregivers are mediated by improvements in (adolescent- and caregiver-reported) family functioning and (adolescent- and caregiver-reported) emotional regulation, and whether treatment effects for adolescents are mediated by improvements in caregiver outcomes.

Our hypotheses are:

i) Adolescents in families assigned to receive the family intervention will show significantly greater improvements in primary and secondary outcome measures compared to the waitlist group, at post-intervention.

ii) Caregivers in families assigned to receive the family intervention will show significantly greater improvements on caregiver-reported secondary outcome measures compared to the waitlist group, at post-intervention.

iii) These improvements for adolescents and caregivers will be maintained at the 3-month follow-up time point for the treatment condition.

iv) In the waitlist families who receive the intervention in a group format, we predict that there will be significant within-group improvements on outcome measures.

### Setting

The study will be implemented by three implementing organisations (i.e. three sites) operating in two governorates of Lebanon—primarily in urban areas in North Lebanon (War Child Lebanon [WC], Danish Refugee Council Lebanon [DRC]) and in informal tented settlements in agricultural areas in north Beqaa (Terre Des Hommes Italy [TDH], Lebanon). Each implementing organisation has existing child protection programming in these areas.

Lebanon is a middle-income country with a recent history of internal and external armed conflict, facing an unprecedented economic crisis, exacerbated by the COVID-19 pandemic and the Beirut port explosions which caused mass devastation in the capital city. Lebanon also hosts the highest number of refugees per capita—with a current estimate of 1.5 million Syrian refugees, in addition to large numbers of Palestinian refugees, in a total national population of 5.9 million [6]. The current political paralysis, economic crisis, and this rapid and large increase in the population over a short period of time have meant that the ability to meet educational, health, financial, and mental health needs of the population is severely limited. Since the onset of the devaluation of the Lebanese Lira, over three quarters of the population are living in poverty with frequent shortages of fuel, essential medicines, and electricity [7]. The situation in Lebanon has taken its toll on the population, including soaring rates of mental ill health, suicide, and child protection violations [8]. Prior to the crisis, estimates indicated there were only 1.26 psychiatrists and 3.42 psychologists per 100,000 population, with 97% working in the private sector, making mental health care inaccessible to the most vulnerable [9].

### Participants

Families will be included if they meet the following inclusion criteria: (i) have an adolescent aged 12–17 years (male and female), (ii) are identified as medium to high risk for child protection concerns by the implementing organisation, (iii) give assent and parental/legal guardian consent to take part in trial procedures, and (iv) at least one adolescent scores above the cut-off on the Pediatric Symptom Checklist (PSC-17) for general psychological distress at screening. Families of any nationality and background will be eligible (with an expected focus on Lebanese, Syrian, and Palestinian families), as well as families of any composition (including single or dual headed households), provided that an adult legal guardian is present. Child protection risk status will be established as part of usual screening and outreach processes for focused psychosocial support by staff in implementing organisations, who will identify and refer potential participants. Medium-to-high risk is defined for this study as being ‘vulnerable to a protection risk but not high with imminent risk’.

Participants will be excluded if they meet any of the following criteria: (i) imminent risk requiring immediate case management at the time of recruitment, or if they have severe psychiatric disturbance or risks requiring specialist mental health services (assessed by implementing organisations as part of usual routine assessment and referral systems); (ii) unaccompanied, separated, or married, due to challenges with the legal consent of guardians; and (iii) engaged in case management at the time of outreach, as those in case management are likely to be receiving sufficient services. If the need for case management arises during the intervention, then families can be referred as usual and remain in the study.

### Sample size

The sample size calculation was based on a two-group comparison of primary outcome at the post-intervention time point. Assuming a 5% two-tailed significance test, 80% power, it is estimated that data from 270 participants would need to be available at the post-intervention time point in order to detect an effect size of .25. Allowing for 30% attrition, this would correspond to an overall sample size of 351 required at enrolment. A recent individual patient data meta-analysis [10] of psychosocial support interventions for children in low-resource humanitarian settings found an effect size for post-traumatic stress symptoms of 0.33, and functional impairment of 0.29, with no significant effect for depression and anxiety. While our primary outcome is a measure of broad child psychological symptoms, we felt these estimates were most applicable to our study context. Given the novel family systems approach we are employing, we aimed for a conservative minimal detectable effect of 0.25.

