### Randomisation

Randomisation will occur after T0 assessments are completed and will be stratified by site. The unit of randomisation will be families, and they will be randomly allocated to intervention or waitlist with a 1:1 ratio. The randomisation sequence will be computer-generated by a statistician located outside Lebanon, and independent of the study. It will be generated using Research Randomizer (randomizer.org [14]), a computer-based pseudo-random number generator using the “Math.random” method within the JavaScript programming language as the core methods for generating its random numbers. Families are randomised into the intervention group (see details in the “Intervention” section), or a waitlist condition, to receive the programme after post-intervention assessments (T1). They will receive the programme in a group format to assess the feasibility and acceptability of different delivery formats.

To ensure approximately equal randomisation in case smaller numbers of families per organisation are attained than planned, blocking will be used with block sizes unknown to the research team. An unblinded study coordinator will send participant lists (in order of baseline assessment completion date and time) to the independent statistician on a regular basis during the study enrolment period. The independent statistician will then match the randomly generated allocation sequence to the participant list and send this back to the unblinded study coordinator, who will then share participant allocations with implementing teams.

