### Analysis

All analyses will be detailed in a statistical analysis plan, which will be signed before unmasking the study data set. Data will be downloaded from the Kobo data collection software and imported into statistical analysis software for data management and analysis. Details of data security and storage can be found in ethical protocols, which are available on request. Data will be co-owned by the PIs’ organisations, data sharing agreements will be signed by all organisations and co-investigators, and data will be made available on request. All study team members meeting criteria for authorship will be invited to co-author papers presenting the findings.

To determine comparability between the conditions at baseline, multiple planned comparisons will be conducted for continuous variables and chi-squared tests for categorical ones; significance testing will be adjusted for multiple comparisons.

An intent-to-treat analysis approach will be used to test for statistically significant differences over time on primary and secondary outcomes between the two conditions. Hierarchical linear modelling (HLM) will be conducted for each continuous outcome, using a group × time interaction analysis. HLM allows the number of observations to vary between participants and effectively handles missing data. Time (linear and quadratic), treatment condition, and their interaction will be included in the models. Fixed effects parameters will be tested for intervention conditions, and time of assessments at 95 % confidence intervals. Level 1 of the model will represent within-patient change over time on the outcomes of interest, and level 2 of the model will include variables in which the patients are nested to provide better estimates of the within-patient change over time. Covariates will be added and model fit parameters will be used to determine the best fitting models for our data.

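### The 270 analysed participants give about 53% power, not 80%, for an effect size of 0.25 on the calculation the protocol describes

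*Protocol article*

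**What the plan says.** The Sample size section gives all the inputs of a standard calculation.

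- Basis: "The sample size calculation was based on a two-group comparison of primary outcome at the post-intervention time point".
- Error rates: "Assuming a 5% two-tailed significance test, 80% power".
- Result: "data from 270 participants would need to be available at the post-intervention time point in order to detect an effect size of .25".
- Enrolment: "Allowing for 30% attrition, this would correspond to an overall sample size of 351 required at enrolment".
- Rationale: the section cites pooled effects of 0.33 (post-traumatic stress symptoms) and 0.29 (functional impairment) from a meta-analysis and then says "we aimed for a conservative minimal detectable effect of 0.25".

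The Randomisation section says of families that "they will be randomly allocated to intervention or waitlist with a 1:1 ratio". The Screening section has one index adolescent per family complete the outcome measures, so participants and randomised units coincide.

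The Analysis section plans a different model from the one used for sizing: "Hierarchical linear modelling (HLM) will be conducted for each continuous outcome, using a group × time interaction analysis". The Sample size section does not refer to that model, and it gives no baseline-to-T1 correlation or other reduction in variance.

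**The concern.** The number of participants looks roughly half of what the inputs printed beside it require. If so, the trial is presented as having 80% power for a small effect when, on its stated basis, a true effect of that size would be missed almost as often as found. The detectable effect would also be larger than the published effects the authors chose as most relevant, so calling 0.25 conservative would be the reverse of the truth. The practical risk is in reading a null result: anyone relying on the stated 80% could take a non-significant primary test as good evidence against an effect of 0.25.

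**Working it through.** **Inputs.** Standardised difference d = 0.25, two-sided α = 0.05, power 80%, comparison at T1 (all Sample size); 1:1 allocation (Randomisation). The effect size is taken as a difference in means in SD units, as the comparison with 0.33 and 0.29 implies.

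**Attempt to reproduce 270.**

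n per arm = 2 × ((1.960 + 0.842) / 0.25)² = 251.2, so 252 per arm and 504 in total. The t-based calculation gives 252.1 per arm; rounded up, that is 253 per arm and 506 in total. The stated 270 is 270/506 = 53% of this.

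**Other readings tried.**

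| Reading | Total needed, or result |
|---|---|
| One-sided 5% | 396 |
| Cohen's f = 0.25 (d = 0.5) | 128 |
| One-sample or paired d = 0.25 | 128 |
| d = 0.29 | 374 |
| d = 0.33 | 290 |
| 270 per arm | about 83% power, but enrolment does not fit |

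The last reading fails because 270 × 1.3 = 351, and the section calls 351 the overall enrolment. So 270 is a total. None of these readings gives 270.

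**Power and detectable effect with 270 analysed (135 per arm).**

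- Power at d = 0.25: 53.7% (normal approximation), 53.5% (noncentral t).
- Detectable d at 80% power: (1.960 + 0.842) × √(2/135) = 0.341; t-based 0.342.

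**With the protocol's own attrition.** The enrolment figure multiplies 270 by 1.3 instead of dividing by 0.7 (270/0.7 = 386). A 30% loss from 351 therefore leaves 351 × 0.7 = 245.7, about 246 (123 per arm). This is a separate slip, but it lowers the power further:

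- Power at 0.25: 49.7%; at 0.29: 62%; at 0.33: 73%.
- Detectable d at 80% power: 0.359.
- Half-width of the unadjusted 95% confidence interval: 1.96 × √(2/123) = 0.25 SD.

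**What baseline adjustment could recover.** Let r be the correlation between baseline and T1 PSC-35 scores. The protocol does not give r, so a range is shown. ANCOVA multiplies the variance by (1 − r²); a change-score contrast multiplies it by 2(1 − r). Power at d = 0.25 with 270 analysed (normal approximation):

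| r | ANCOVA | Change score |
|---|---|---|
| 0.3 | 58% | 41% |
| 0.4 | 61% | 47% |
| 0.5 | 66% | 54% |
| 0.6 | 73% | 63% |
| 0.7 | 82% | 76% |

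Correlation needed for 80% power:

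- ANCOVA: √(1 − 270/506) = 0.68 at 270; √(1 − 246/506) = 0.72 at 246.
- Change score: 1 − (270/506)/2 = 0.73 at 270; 1 − (246/506)/2 = 0.76 at 246.

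**The case against.** The best defence is that 53% is the power of an unadjusted comparison at T1, whereas the Analysis section plans a group-by-time hierarchical model with covariates. Actual power then depends on r and could be well above 53%. A journal article also condenses a fuller protocol, where a correlation may be recorded.

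Part of this stands. The trial's actual power is not shown to be 53%, and the comparison with the benchmarks depends on the unadjusted analysis: under ANCOVA with 270 analysed, the detectable effect is already 0.342 × √(1 − 0.3²) = 0.326 at r = 0.3, just below 0.33. How a null result would be interpreted is also not written anywhere in the article, so that consequence is a risk rather than a stated plan.

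It does not rescue the paragraph. Condensing excuses an omission, but here a printed result contradicts the inputs printed with it, and the section names a two-group comparison at T1 as its basis. The correlation required is also demanding. A group-by-time term with two time points and a freely estimated baseline difference behaves like a change score, which gains nothing at r = 0.5 and needs 0.73. The design works against a high r: entry requires a PSC-17 score of 12 or more (Screening), those 17 item scores are reused in the baseline PSC-35 (Primary outcome), and T1 is about 10 weeks after T0 (Outcome measures). Selecting on part of the baseline score narrows its range, which tends to lower the correlation.

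**Conclusion.** The concern holds. On the basis the protocol states, 80% power for 0.25 needs 504 to 506 analysed, not 270. With 270, power is about 53% and the detectable effect is 0.34; with the 246 left after 30% attrition from 351, the figures are about 50% and 0.36. This rests on the effect size being a standardised mean difference, on 1:1 allocation, and on an analysis without baseline adjustment, as the Sample size section describes. With baseline adjustment power may be higher, but 80% at 270 requires a correlation of at least 0.68 (ANCOVA) or 0.73 (change score), which is nowhere assumed. As written, 0.25 is not a conservative minimal detectable effect.

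**What to change.** Rewrite the Sample size paragraph in one of two ways.

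1. If the calculation really was an unadjusted comparison at T1: state that 270 analysed gives 80% power for a standardised difference of 0.34 and about 53% for 0.25, and remove the claim that 0.25 is a conservative minimal detectable effect.
2. If a baseline-adjusted analysis was intended: name the method, so that it matches the primary model in the Analysis section, state the assumed baseline-to-T1 correlation and its source, and give power over a range of correlations. The table above supplies this for ANCOVA and for a change score. The row used should be the one that corresponds to the planned group-by-time model.

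In either case, give the figures for the number expected after attrition as well as for 270, and state that a non-significant primary result will be read from the confidence interval (half-width about 0.25 SD, unadjusted, at 246 analysed). The statistical analysis plan, which the protocol says will be signed before unmasking, is a natural place to record the correction.

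The cost is rewording one paragraph and accepting a less favourable statement of sensitivity. No further participants are asked for; the protocol version is dated 31 March 2022 and recruitment was expected to end in April 2022.

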### Screening

After obtaining informed consent and assent, the research assistant will record family demographic data and administer the screening interview over the telephone with each adolescent aged between 12 and 17 years old. Localised guidance [11] to assess participants over the phone and in cramped living spaces will be followed to maximise the privacy of respondents during assessments and to respond to distress or discomfort.

The screening interview with adolescents will consist of the PSC-17 (adolescent report), a brief version of the 35-item PSC measuring symptoms of internalising and externalising difficulties in children and adolescents [12]. The tool has been validated with young adolescents in Lebanon, using semi-structured interviews with psychiatrists as the gold standard [13], and a cut-off of 12 or more is indicative of a need for psychosocial treatment. The family will be eligible to take part if at least one adolescent screens positive on the PSC-17. Where more than one adolescent screens positive, the adolescent scoring the highest will be selected as the index adolescent, and only this adolescent will complete outcome measures at T0 and remaining time points. In the unlikely event of multiple adolescents in the same family scoring the same total score, the oldest will be selected as the index adolescent.

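### The 30% attrition allowance is applied as 270 × 1.3 rather than 270 / 0.7, so 351 enrolled leaves about 246 at T1, not the required 270

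*Protocol article*

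**What the plan says.** The Sample size section of the protocol article builds the target in two steps.

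- The analysed sample: "The sample size calculation was based on a two-group comparison of primary outcome at the post-intervention time point". The test is specified as "Assuming a 5% two-tailed significance test, 80% power", and the text concludes that "data from 270 participants would need to be available at the post-intervention time point" "in order to detect an effect size of .25".
- The enrolment target: "Allowing for 30% attrition, this would correspond to an overall sample size of 351 required at enrolment".

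No other basis is given for 351. Under Randomisation, families are the unit and "they will be randomly allocated to intervention or waitlist with a 1:1 ratio". Under Screening, where several adolescents in a family screen positive, one is chosen as the index and "only this adolescent will complete outcome measures at T0 and remaining time points". One family therefore contributes one adolescent to the primary outcome, and families and participants can be counted interchangeably.

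**The concern.** The first step fixes how many participants must have T1 data. The second should give the number to enrol so that this many remain after the assumed loss. A loss of 30% is a fraction of those enrolled, so the analysed number has to be divided by 0.7. Adding 30% of the analysed number instead gives a target that is too small.

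At stake is whether the trial meets its own requirement when everything goes as planned. 351 is the only enrolment target in the document and the power claim depends on it. The error runs in the flattering direction: it makes the trial look better protected against loss to follow-up than it is, in a setting that the Setting section itself describes as unstable.

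**Working it through.** **Inputs** (Sample size section unless noted)

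- Needed with T1 data: 270 in total
- Attrition: 30%
- Enrolment target: 351
- Two-sided alpha 0.05, power 80%, effect size 0.25, read here as a standardised mean difference
- Allocation 1:1 (Randomisation)
- One index adolescent per family (Screening)

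**Reproducing the plan's figure**

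- Analysed number × (1 + attrition): 270 × 1.30 = 351.0, an exact match.
- Analysed number / (1 − attrition): 270 / 0.70 = 385.7, rounded up to 386. This does not match.

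So 351 comes from multiplying by 1.3.

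**What 351 delivers**

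- Expected with T1 data: 351 × 0.70 = 245.7, about 246.
- Shortfall: 270 − 245.7 = 24.3, and 24.3 / 270 = 9%.
- Largest attrition at which 270 remain: 1 − 270/351 = 23.1%.
- Enrolment consistent with 270 and 30%: 386, since 386 × 0.70 = 270.2. That is 35 above 351, about 10%.

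**Cost in power of this step alone**

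*If 270 is accepted as giving 80% power.* The standardised signal at 270 is 1.960 + 0.842 = 2.802 and scales with the square root of the sample size. At 246 it is 2.802 × √(246/270) = 2.674. Power = Φ(2.674 − 1.960) = Φ(0.714), about 76%. The effect detectable with 80% power moves from 0.25 to 0.25 × √(270/246) = 0.26.

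*If the stated inputs are taken literally.* For an unadjusted two-sample t-test with equal arms:

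| With T1 data | Per arm | Power at 0.25 | Effect detectable with 80% power |
|---|---|---|---|
| 270 | 135 | 53.5% | 0.342 |
| 246 | 123 | 49.7% | 0.359 |

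On either basis the attrition step costs about 4 percentage points.

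The gap between 80% and 53.5% has a different cause: 270 does not follow from the stated inputs. An unadjusted comparison at 0.25 needs about 252 per arm, 504 in total. Reaching 270 would need a reduction in variance that the article does not state. Baseline adjustment would do it if the baseline-to-T1 correlation were √(1 − 270/504) = 0.68; assumed correlations of 0.5 and 0.7 give totals of 378 and 258. Correcting the attrition step therefore does not show that 270 is adequate.

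**The case against.** The arithmetic itself is not open to dispute, but three objections deserve an answer.

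1. **The absolute powers near 50% mix two problems.** Almost all of the distance from 80% to 49.7% belongs to the basis of 270, and those powers assume no gain from baseline, although the Analysis section plans a group-by-time model that includes it. This stands as a caution about reading the table: only the difference between its rows belongs to the attrition step. It does not remove that difference, which is about the same if 270 is taken at face value.

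2. **The effect is moderate and conditional.** The 30% is an allowance, and at 23.1% loss or less 351 still yields 270. The error does not touch the estimand, the analysis or the type I error. All of that is true. The plan nevertheless chose 30% as the loss to be protected against, and at 30% its target fails.

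3. **The planned model copes with missing data.** The Analysis section says that hierarchical modelling handles varying numbers of observations. That concerns estimation. The sample size requirement is expressed as T1 data in hand, and the model does not restore the missing T1 observations.

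Reading the 30% as a share of completers does not help either. It would mean 81 lost out of 351, which is 23.1% attrition and not the 30% stated. Nor can a second adolescent in the family fill the gap, since only the index adolescent completes outcome measures.

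**Conclusion.** The concern holds. The figures 270, 30% and 351 are mutually inconsistent. At the planned attrition the trial ends with about 246 participants with T1 data, 24 (9%) below its stated requirement, and 351 covers no more than 23.1% loss.

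The counts rest only on numbers in the Sample size section. The power figures rest on equal arms and on one of two assumptions: that 270 gives 80% power (then about 76% at 246), or that the test is an unadjusted comparison at a standardised difference of 0.25 (53.5% falling to 49.7%). The effect on power is moderate, but this is the trial's primary sample size statement and it is wrong as written.

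**What to change.** Replace the attrition sentence with one of two consistent statements:

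- 351 enrolled retains 270 with T1 data provided attrition does not exceed 23%; or
- 351 enrolled with 30% attrition retains about 246 with T1 data.

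The second keeps the plan's own attrition assumption. The first changes it, so the authors should say why 23% is realistic. Whichever number is kept should be carried into the power statement.

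Keeping both 270 and 30% would imply 386 enrolled, but no extra enrolment is asked for here. By the article's version date of 31 March 2022, recruitment was expected to end in April 2022, and an accurate statement of what 351 provides is enough.

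The attrition correction takes one sentence, and the stated position becomes slightly less favourable. A sound power figure for 246 or 270 also needs the basis of 270 to be settled, so the two corrections are best made together.
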